## Drug administration

After laboratory tests have been completed and all the eligibility criteria are met, the participant can be enrolled. After enrollment and assignment of as participant ID number, the participant will be escorted to the study pharmacy. Drug assignment will be made as described in the randomization section. The drug doses are as follows:

Chloroquine 10 mg/kg on days 0 and 1; 5 mg/kg on day 2 (to the nearest ¼ tablet)

Artesunate approximately 4 mg/kg on days 0, 1 and 2

Azithromycin 30 mg/kg on days 0, 1 and 2

Atovaquone-proguanil approximately 15-20 mg/kg on days 0, 1 and 2 (as described in the study intervention section and directed in the package insert)

Participants will be observed for at least 30 minutes to monitor for adverse reactions and to make sure the medicine is not vomited. All drug administration attempts and episodes of vomiting will be recorded on the CRF. The procedure for drug administration will be as follows:

1. Administer dose of chloroquine and observe for 30 minutes.
   1. If vomiting does not occur, go to step 2
   2. If vomiting occurs after first dose, repeat dose
   3. If vomiting occurs after second dose, consult a clinician or investigator
   4. If the clinician determines that the child appears well enough to continue with oral therapy, repeat dose
   5. If third dose is vomited within 30 minutes, transport to hospital for evaluation and parenteral therapy.
      1. If this sequence of events occurs on day 0 of the enrollment illness, the participant will be removed from the study
      2. If this sequence of events occurs on day 1 or 2 of the enrollment illness or during subsequent treatment episodes, the participant will continue in the study
2. If the participant has tolerated the chloroquine and is assigned to receive combination therapy, administer the partner drug next.
   1. If vomiting does not occur, administration complete
   2. If vomiting occurs after first dose, repeat dose
   3. If vomiting occurs after second dose, consult a clinician or investigator
   4. If the clinician determines that the child appears well enough to continue with oral therapy, repeat dose
   5. If third dose is vomited within 30 minutes, do not administer drug again and note on CRF
      1. If this sequence of events occurs on day 0 of the enrollment illness, the participant will be removed from the study
      2. If this sequence of events occurs on day 1 or 2 of the enrollment illness or during subsequent treatment episodes, the participant will continue in the study. A clinician will assess if the child requires transportation to the hospital for further evaluation and therapy.

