### Reasons for Withdrawal

Participants will be removed from the study if:

- Any clinical adverse event (AE), laboratory abnormality, intercurrent illness or other medical condition occurs such that continued participation in the study would not be in the best interest of the subject
- If the participant requires chronic antimicrobial therapy. For example, children who are found to be infected with HIV will be referred for trimethoprim-sulfamethoxazole prophylaxis and anti-retroviral eligibility evaluation and removed from the study
- Participants who miss ≥ 2 consecutive routine visits will be removed from the study

Participants may withdraw voluntarily from the study at any time.

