### Handling of Withdrawals

Participants who withdraw from the study with on-going AEs will be asked to return for follow-up. Specialized tracers have been designated to help to locate participants who do not return for follow-up visits. They will go to the house of the participant (directions are given at enrollment) and try to find the participant or a family member. The staff members will return to try to find any participant who missed a scheduled visit. If the participant is not available, the staff member will ask about the child’s general health, if it is known.

We anticipate some children will not complete the full year of follow-up either due to migration or voluntary withdrawal, so we have chosen to enroll an excess of participants to allow for this loss. Participants who leave the study prematurely will not be replaced.

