Appendix II: Expected adverse reactions to study drugs

|  | Common adverse effects | Management of adverse effects | Rare adverse effects |
| --- | --- | --- | --- |
| CQ(32) | Pruritis  Nausea  Diarrhea  Dizziness | Repeat dose if vomiting occurs (total of 3 attempts) | None reported except for chronic administration (for weekly prophylaxis or treatment of rheumatoid disease) |
| AS(43) | Dizziness (15%)  Nausea (16%)  Vomiting (11%)  Diarrhea (34%)  Anorexia (1%)  Cannot distinguish these effects from underlying malaria disease | Repeat dose if vomiting occurs (total of 3 attempts) | Decreased reticulocyte count  Slight elevation of transaminase  Anaphylaxis |
| AP (Malarone package insert) | Vomiting (10%)  Pruritis (6%)  Diarrhea (6%)  Elevated transaminases (noted in Thai adults)-resolved spontaneously | Repeat dose if vomiting occurs (total of 3 attempts)  Follow transaminase level. Discontinue enrollment in study if abnormality does not resolve by next treatment episode. | Cutaneous reaction  Seizure and psychotic events (causal relationship not established) |
| AZ (Zithromax package insert) | Diarrhea (2.6%)  Abdominal pain (1.7%)  Vomiting (2.3%)  Nausea (0.4%)  Rash (0.6%) | Repeat dose if vomiting occurs.  Evaluate if rash occurs | Anemia  Leukopenia  Headache  Hyperkinesis  Dizziness  Agitation  Nervousness  Edema  Fever  Fungal superinfection  Cough  Urticaria  conjuctivitis |

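### Day-0 vomiting removes children after the arm is assigned, through one drug step on monotherapy but two on each combination, and one removal rule is written for the AP arm only

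*Protocol*

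**What the plan says.** The Drug administration section (between 7.2 and 7.3) sends the enrolled child to the pharmacy, where "Drug assignment will be made as described in the randomization section". Dosing follows, so anything that happens at dosing comes after allocation.

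Step 1 is chloroquine, for everyone. Step 2 is conditional: "If the participant has tolerated the chloroquine and is assigned to receive combination therapy, administer the partner drug next". Each step allows up to three attempts. Each has the same trigger, "If third dose is vomited within 30 minutes", and the same day-0 consequence: "If this sequence of events occurs on day 0 of the enrollment illness, the participant will be removed from the study".

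For a failure on day 1 or 2 of the enrolment illness "or during subsequent treatment episodes, the participant will continue in the study".

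Four other places bear on this:
- Section 5.4.3 allows discretionary removal in any arm for an adverse event or laboratory abnormality "such that continued participation in the study would not be in the best interest of the subject".
- Section 5.4.4: "Participants who leave the study prematurely will not be replaced".
- Section 6.7 provides rescue treatment for children who cannot complete a regimen because of adverse events. It states that treatment given by the study team or the research ward does not cause removal, and it makes no day-0 exception.
- Appendix II, in the atovaquone-proguanil (AP) row only, says of transaminases: "Discontinue enrollment in study if abnormality does not resolve by next treatment episode". The artesunate row also lists raised transaminase but has no such instruction.

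Section 11.3 counts, for the primary endpoint, only the time a child is on study.

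**The concern.** The primary question is whether each combination lowers annual malaria incidence relative to chloroquine alone. That contrast is protected by randomisation only if children stay in it regardless of what their assigned drugs do to them. Here a combination child who has kept chloroquine can still be dropped because of the partner drug. A monotherapy child cannot be dropped at that point. If children who vomit repeatedly differ in their later malaria risk, the retained combination children are a selected group and the monotherapy children are not selected in the same way.

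The AP transaminase rule acts later and more mildly. The child's earlier person-time is kept, but follow-up stops for a reason written for one arm only. If that reason is related to malaria risk or to the number of treated episodes, the censoring is informative.

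An analysis plan can define who is analysed, but it cannot recover episodes that were never observed because follow-up ended.

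**Working it through.** **1. The plan's own sample size, to see whether it is affected.** Section 11.2 inputs: 1.5 against 1.0 episodes per year, Poisson, two-sided alpha 0.05/3, 90% power. With the Poisson-regression formula (Signorini) and equal allocation:

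N = (2·z_a + z_b·√(2 + 2/RR))² / (1.5·(ln RR)²), with RR = 2/3, z_a = 2.394, z_b = 1.282

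N = (4.788 + 2.866)² / (1.5 × 0.1644) ≈ 237.5 in total, or 119 per arm. The protocol states 120. Allowing 25% loss, 120/0.75 = 160. Both figures are reproduced, and neither changes with this point.

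**2. Day-0 removal hurdles by arm**

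| Arm | Chloroquine step | Partner step |
|---|---|---|
| Chloroquine alone | yes | none |
| Each combination | yes | yes |

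The first column is common to all arms. Only the second differs by design.

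**3. Expected removals at the partner step.** The protocol gives no rate for three consecutive vomits. Appendix II lists vomiting at 11% (artesunate), 10% (AP) and 2.3% (azithromycin). The background Safety section gives 2-4% for azithromycin. Treating the listed rate p as the chance of vomiting a first attempt (assumption), removals per 160 are 160·p³ if attempts are independent and 160·p if one vomit always means three. An intermediate case assumes that each repeat attempt is vomited with probability 0.5, giving 160·p·0.25.

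| Arm | p | Independent | Repeat 0.5 | Fully correlated |
|---|---|---|---|---|
| Artesunate | 0.11 | 0.2 | 4.4 | 17.6 |
| AP | 0.10 | 0.2 | 4.0 | 16.0 |
| Azithromycin | 0.023 | 0.002 | 0.9 | 3.7 |
| Azithromycin | 0.04 | 0.01 | 1.6 | 6.4 |
| Chloroquine alone | no step | 0 | 0 | 0 |

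**4. Effect on the primary comparison when there is no true difference.** Let f be the share removed at the partner step and r the malaria incidence in removed relative to retained children. Both are assumed. If the whole arm would have had 1.5 episodes per year, the retained children have m = 1.5/(1 − f + f·r), so the apparent rate ratio is 1/(1 − f + f·r). The rejection probability uses the difference 1.5 − m, standard error √((1.5 + m)/120) and critical value 2.394. The nominal level is 0.0167.

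| f | r | Apparent rate ratio | Rejection probability |
|---|---|---|---|
| 0.1% | 2 | 0.999 | 0.0167 |
| 2.5% | 2 | 0.976 | 0.020 |
| 10% | 2 | 0.909 | 0.066 |
| 10% | 3 | 0.833 | 0.229 |

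Example for the second row: m = 1.5/1.025 = 1.463; difference 0.037; standard error √(2.963/120) = 0.157; ratio 0.233; the two tails beyond ±2.394 sum to about 0.020. With r = 1 there is no bias. With r below 1 the combination would look worse instead of better.

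**5. The texts side by side.** On day 0 the child leaves the study. On days 1-2, and in later episodes, the child stays. Section 6.7 says treatment by the team or ward does not lead to removal. Section 11.3 already counts smear-verified episodes treated with non-study drugs at the referral hospital, so the primary endpoint does not require that every episode receive study drug.

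**The case against.** The strongest reply is that a day-0 failure is not the same event as a day-1 or day-2 failure. On day 0 the child has retained none of that drug, and a child who fails chloroquine goes to hospital without having started study treatment. Leaving out never-started children is a recognised choice, and persistent vomiting is already an exclusion criterion at enrolment. This has some force for the chloroquine step. It has less at the partner step, where the child has kept chloroquine and the new exposure is the drug that randomisation assigned.

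The second reply is size, and it stands. With independent attempts the expected loss is a fraction of one child per arm. Two filters push it down further: the enrolment exclusion, and the requirement that chloroquine was kept before the partner drug is tried. Nothing in the protocol links repeated vomiting to annual malaria incidence, and 40 losses per arm are allowed for in any case.

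A reader might infer that the rule erases intolerance from the safety comparison in the combination arms only. The protocol does not support that. Chloroquine vomiting removes children in every arm, and vomiting and administration attempts are recorded on the CRF. Adverse events are documented, and section 7.5 provides an early termination visit. What is lost is later follow-up. Nor can every removal be called drug intolerance, because Appendix II says the effects listed for artesunate cannot be separated from the malaria itself.

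A reader might also treat the AP rule as a loss of the randomised child. It is not: person-time before removal is counted, and section 5.4.3 already permits laboratory-based removal in all arms. What remains is that a specific instruction is written for one arm.

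**Conclusion.** The point holds as a defect of design and consistency, not as a demonstrated bias. Removal after allocation depends partly on the assigned arm, the removed children drop out of the primary comparison, and the day-0 rule does not fit the day 1-2 rule or section 6.7. The AP row adds arm-specific, possibly informative censoring.

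The likely effect is small. At 2.5% removed, with double the incidence in those removed, the error rate moves from 0.0167 to about 0.020. Clear inflation needs about 10% removed, which requires nearly complete correlation between attempts on artesunate or AP, and raised incidence in those removed. Azithromycin cannot reach that on its listed rates. These figures rest on assumed correlation and assumed incidence ratios, and the direction is unknown. The stronger statement, that the comparison with monotherapy is broken, goes beyond what the protocol shows. The case for changing the text is that the correction is cheap and must be made before the data are lost.

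**What to change.** Reconcile sections 5.4.3, 6.7, Drug administration, 11.3 and Appendix II so that not receiving, or stopping, study drug is a separate matter from ending follow-up. Suitable wording: *A participant who does not receive or who stops study drug remains in scheduled follow-up if the guardian agrees. Episodes and person-time are counted in the assigned arm for the primary analysis.* State that day-0 vomiting removals, or the corresponding treatment stops once the text is changed, will be reported by arm and by drug step, and do the same for stops due to transaminases.

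This proposes no rule for handling vomiting or raised transaminases, or for whether study drug is given at a later episode. Those decisions stay with the investigators.

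Cost: a short amendment, follow-up of probably a few more children, and slight dilution of the contrast from children who kept no partner drug at enrolment. The sample size stays at 160 per arm.

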## Follow-up

Follow-up visits may be one of four types: day of new malaria episode diagnosis, drug efficacy follow-up, routine visit, unscheduled visit.

On the initial day of a new diagnosis, a venipuncture will be performed to obtain the following studies: filter paper sample for molecular analysis, CBC, ALT, creatinine, chloroquine level and specimen for cryopreservation of parasites. The total volume will be approximately 3.5-5 mL.

Drug efficacy follow-up occurs after the initial and all subsequent administrations of the study drug to treat symptomatic malaria. Visits will occur on days 1, 2, 3, 7, 14, 21, 28. Hemoglobin, malaria smears and filter papers will be obtained on each of those days and a physical examination will be completed. Specimens from a finger prick will be obtained on two occasions after day 0: on day 14 and an additional day assigned randomly at enrollment. Chloroquine level, CBC, ALT and creatinine will be measured routinely on day 14, after acute changes associated with malaria should have resolved If the participant misses the visit corresponding to the day a chloroquine level and/or CBC, ALT and creatinine arescheduled to be collected, the study team will endeavor to collect this specimen as the next visit. Drug administration will occur on days 1 (2nd dose) and 2 (3rd dose).If treatment failure occurs after day 3 and the parasite density is >10,000/mm3, blood will be collected to measure the chloroquine level and for cryopreservation of malaria parasites for further in vitro susceptibility testing. A neurologic exam will occur on day 28.

Routine visits occur every four weeks. Malaria smear and filter paper will be obtained. The malaria smear will be read at that time only if there are complaints of an illness or the clinician suspects malaria. The encounter will include an interval history, questions about off-study drug use, recent travel, bed net use and a physical examination. At routine visits 4, 8 and 13, CBC, ALT and creatinine will be obtained for safety monitoring surveillance. All blood specimens will be collected from a finger prick except for the specimens for cryopreservation which require 3-5 ml. On all other days, the amount of blood drawn from the finger prick will range from 0.05 ml (malaria smear, hemoglobin, filter paper) to approximately 0.5 ml (malaria smear, hemoglobin, filter paper, CBC, ALT, creatinine and chloroquine level).

Unscheduled visits are expected to occur numerous times during the one year of follow-up since children in this region suffer from many acute illnesses including malaria, respiratory disease and diarrhea. During unscheduled visits, the participant will be evaluated according to standardized procedures. Any signs or symptoms of malaria will prompt the collection of a malaria smear and hemoglobin measurement. If the participant is diagnosed with malaria, he or she will receive the treatment assigned on enrollment. Further evaluation and management will be undertaken by the study team according to national guidelines.

### Cases of malaria during follow-up period

If symptomatic malaria recurs within 14 days of the initiation of study treatment, rescue therapy will be given and the episode will be coded as an early treatment failure or late clinical failure. If an illness episode occurs more than 14 days after the initiation of the last treatment, it will be considered to be a new clinical episode and treated with the study drug. The case definition of uncomplicated malaria for new clinical episodes is a positive malaria smear and any of the following signs or symptoms:

- Fever measured at the clinic
- History of fever in the past 24 hours
- Vomiting
- Abdominal pain
- Poor oral intake
- Headache
- Irritability for at least 12 hours

Any participant who has danger signs or signs of severe disease (as described above) including a parasite density greater than 10% or greater than 500,000/mm3 will not be treated with the study drug and will be transported to Queen Elizabeth Central Hospital for further management.

### Rescue therapy

Rescue therapy refers to medication to treat malaria when it is not appropriate to give the study drug. This includes episodes of treatment failure within 14 days of the first administration of the study drug or any case of severe malaria. Rescue therapy will be administered according to the national treatment policy of Malawi for uncomplicated or severe malaria as appropriate. At this time, Malawi is in the process of selecting which artemisinin-based combination therapy will be its first line therapy. Once the decision has been made, we will follow that policy.

## Final Study Visit

The final study visit will occur on the 13th routine visit unless the participant is actively enrolled in drug efficacy follow-up or an unresolved AE remains. If the participant has not yet completed the drug efficacy follow-up, the final study visit will occur on day 28 of the drug efficacy trial or when the endpoint is reached. For participants who have unresolved AEs, follow-up will continue until the AE is resolved or stabilized.

## Early Termination Visit

If early termination occurs, and the participant is willing, the procedures associated with a routine visit will be performed. In addition, CBC, ALT and creatinine will be obtained and a neurological examination will be performed if they were not done in the past four weeks. If the participant has not completed the scheduled chloroquine level ascertainment, the chloroquine level will be measured at that time, as well.

# Study Procedures/Evaluations

Refer to Appendix I for the Schedule of Events

## Clinical Evaluations

*History-comprehensive*

- The medications administered to the child in the past week
- Any underlying medical conditions
- Allergies
- Recent travel history and bed net use

*History-possible adverse drug reactions and interval*

A standardized checklist in the case report form includes symptoms of malaria, as well as most common adverse effects of the drugs being administered.

*Questioning about antimalarial use*

The parent/guardian will be asked if any drugs have been administered to the child in the interval since the last visit. The clinician will then specifically ask about the commonly administered antimalarial drugs.

*Physical examination*

The physical examination includes vital signs (temperature, heart rate, respiratory rate), weight, height and a complete physical examination that focuses on: signs of malaria, signs of non-malaria sources of fever and adverse reactions to the medications.

*Neurological examination*

A basic age-appropriate neurological examination will be conducted at the end of every episode of malaria treatment if the participant is not ill (day 28) and also at visit number 4, 8 and 13. See appendix IV.

## Rescue therapy

Rescue therapy will be administered if the participant develops early treatment failure or late clinical failure within the first 14 days after the initiation of therapy. Rescue therapy will be administered according to the national treatment guidelines in Malawi. Participants who develop signs or symptoms of severe malaria, or are deemed too ill to receive oral therapy, will be transferred to the Queen Elizabeth Central Hospital research ward for parenteral therapy.

## Laboratory Evaluations

### Clinical Laboratory Evaluations

*Malaria smears*

Both thick and thin smears will be obtained during the study. Parasite density will be quantified each time malaria smears are obtained, either at the time of the visit if the participant is ill or at a later time. Standard operating procedures are followed to assure uniform and high quality malaria smears. Thick smears are read by counting the number of parasites seen per 200 white blood cells. Parasite density for days 0 through three will be calculated based on the exact white blood cell count obtained on day 0. Otherwise, quantification will be based on an expected 8,000 white blood cells/mm3.Thin smears are read by counting the number of parasites seen per 500 red blood cells. Exact parasite density is calculated based on the red blood cell count. Thin smears will be used to identify the malaria species each time the diagnosis of malaria is made.

Accurate speciation and quantification will be assured based on Standard Operating Procedures. Slides will be read by at least two readers with a tie-breaker in the case of significant discrepancies. All readers have been trained in malaria diagnostic microscopy using the Malaria Research Reference and Reagent Resource (MR4) standardized slide set designed for this purpose, and, subject to continued availability of the slide set, will be evaluated annually using the slide set to assess their competency.

*Hemoglobin*

Hemoglobin measurement is obtained from the same finger stick as the malaria smear and conducted as a point-of-care test by the nurses.

*Complete blood count*

Complete blood counts will be performed in a Coulter counter. This examination required 20 microliters of blood.

*ALT and Creatinine*

These laboratory results will be obtained from a biochemistry analyzer. This examination requires 30 microliters of whole blood.

*Chloroquine level*

0.5mL specimen will be collected from a finger stick into an EDTA microtainer. The specimen will be transported to the Wellcome Trust laboratory for chloroquine level measurement by high pressure liquid chromatography. . This analysis requires 100 microliters of blood. Two hundred microliters will be taken if possible in case of mechanical malfunction or to preserve for future validation. Some specimens may also be tested in a reference laboratory at the Liverpool School of Tropical Medicine, UK*Special Assays or Procedures*

*Cryopreservation of parasites*. Parasites from the first day of a new malaria episode and any case of late parasitologic failure will be collected from participants via venipuncture. The sample will be transported to the Wellcome Trust Clinical Research Laboratory adjacent to the BMP office on the grounds of Queen Elizabeth Central Hospital in Blantyre for separation of red blood cells for cryopreservation, and storage of serum. The purpose of cryopreservation of parasites is to allow future characterization of the parasites and confirm reduced susceptibility in vitro, in the event that clinical chloroquine resistance emerges. Serum will be used to assess the parasiticidal capacity from participants who have treatment failure.

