## Description

This study is a randomized longitudinal open-label drug efficacy trial among children who present to a government health clinic with uncomplicated falciparum malaria. Otherwise healthy children who are found to have malaria and whose parents/guardians consent to participate in the study will be enrolled in this study for one year. The participants will be randomized to one of the four drug treatment arms: CQ monotherapy, CQ plus artesunate, CQ plus azithromycin, and CQ plus AP. They will continue to receive the same treatment for each new episode of malaria for the next year. If the treatment fails, participants will receive rescue therapy, but will continue in the trial. At the first diagnosis and all subsequent new episodes of malaria, a 28 day drug efficacy study will be completed. Participants will also be asked to return for routine follow-up visit every four weeks.

***Follow-up.*** With enrollment and the first dose of therapy occurring on day 0, participants will be followed actively on days 1, 2, 3, 7, 14, 21 and 28 at the study clinic, and by daily availability of a study clinician to evaluate and treat as needed even if follow-up is not scheduled. At all active and passive follow-up times, malaria smears, hemoglobin and filter paper strips will be obtained and brief history taken and physical examinations made to seek signs or symptoms of persistent or recrudescent malaria and use of any medications outside the protocol.

In addition, participants will attend four-weekly follow-up visits at the study clinic. Weight, height, hemoglobin, temperature and malaria smears and filter papers for later evaluation of asymptomatic disease will be recorded and the participant examined and questioned for signs or symptoms of malaria or other illnesses. Further evaluation, including immediate reading of the malaria smear, will take place if the parent/guardian reports symptoms, if the participant appears ill to the clinic staff or there is a documented fever. All non-malaria illnesses will be treated according to the national guidelines.

Management of early or delayed attendance of these follow up visits is detailed in the Standard Operating Procedure.

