## Definition of treatment outcomes

The 2004 WHO definitions of treatment outcomes will be used as follows:

Therapeutic efficacy will be defined as:

- Early treatment failure (any one of the following)
  - danger signs or severe malaria on days 1, 2 or 3, with parasitemia. Hemoglobin less than 5 without any other signs of severe disease when a participant is receiving therapy will not be a criteria for Early Treatment Failure as hemoglobin levels frequently decrease even with effective therapy.
  - parasitemia on Day 2>Day 0 level
  - axillary temperature > 37.5oC on day 3 in the presence of parasitemia
  - parasitemia on day 3 > 25% of day 0 level
- Late clinical failure
  - development of danger signs, severe malaria or axillary temperature > 37.5oC or a history of fever within the past 24 hours in the presence of parasitemia during days 4-28
  - and no criteria for early treatment failure
- Late parasitologic failure
  - Presence of parasitemia on day 28 without fever
  - and without previously meeting any of the criteria for early treatment or late clinic failure
- Adequate clinical and parasitologic response
  - absence of parasitemia on day 28
  - and without previously meeting any of the criteria of early treatment or late clinical failure

A new episode of malaria will refer to any episode of clinical malaria (symptoms and a positive malaria smear) that occurs more than 14 days after therapy.

If a seizure meets the following criteria of a febrile seizure, the episode will not be considered a danger sign. The following criteria must be met:

1. Occurring in the presence of a reported or documented fever or with a rise in temperature.
2. Generalized seizure witnessed by reliable family member or study staff
3. Duration ≤30 minutes
4. Absence of mental status impairment two hours after the event..
5. Normal neurological examination by a study clinician or investigator within 24 hours of seizure.

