## Rescue therapy

Rescue therapy will be administered to children who develop clinical treatment failure within the first 14 days after a treatment episode or who are unable to complete an adequate treatment regimen due to AEs. Rescue therapy will be recorded on the CRF. Rescue therapy for uncomplicated malaria will be based on the national treatment guidelines in Malawi. For children who develop signs or symptoms of severe malaria, parenteral therapy will be administered at the Paediatric Research Ward at the hospital. Treatment that is administered by the study team or by the Paediatric Research Ward staff after complete evaluation will not lead to removal of the participant.

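### A well child can be an early treatment failure on the day-2 or day-3 parasite count alone, but the rescue sections disagree on that child and the smear rule lets the count be read later

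*Protocol*

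**What the plan says.** **Definition of failure.** Section 4.3 of the protocol lists four criteria for early treatment failure, any one of which is enough. Two are counts only: "parasitemia on Day 2>Day 0 level" and "parasitemia on day 3 > 25% of day 0 level". The other two need danger signs or severe malaria, or fever, together with parasitemia.

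**Rescue.** The trigger is stated in five places:

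- Section 4.2: "If the treatment fails, participants will receive rescue therapy, but will continue in the trial".
- Section 6.7: "Rescue therapy will be administered to children who develop clinical treatment failure within the first 14 days after a treatment episode". It also covers children who cannot complete the regimen because of adverse events.
- Section 7.3.1: "If symptomatic malaria recurs within 14 days of the initiation of study treatment, rescue therapy will be given".
- The rescue paragraph that follows 7.3.1: "This includes episodes of treatment failure within 14 days of the first administration of the study drug or any case of severe malaria".
- Section 8.2: "Rescue therapy will be administered if the participant develops early treatment failure or late clinical failure within the first 14 days".

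**Smear reading.** Section 8.3.1 has parasite density quantified for every smear, "either at the time of the visit if the participant is ill or at a later time". Section 7.3 requires a smear at each efficacy visit (days 1, 2, 3, 7, 14, 21 and 28) but gives no reading time. Sections 4.2 and 7.3 expressly defer reading, unless the child seems ill, only for the routine four-weekly visits.

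**The concern.** A count-only failure is by definition a finding in a child who may look well. The plan acts on it only if two things hold: someone knows the count while the child is at the clinic, and the instructions agree on what the count means for rescue. As written, neither is assured. The general reading rule lets the slide of a child who is not ill wait, and the rescue sections use different triggers.

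Two things are at stake. One is patient safety: a rising or slowly falling count is an early sign that treatment may not be working, and it could go unseen until after the child has left. The other is consistency. The trial is open label, and the protocol's rationale describes partner drugs that differ in how fast they act. Two children with the same count could be handled differently according to which section staff follow.

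**Working it through.** No sample size, power or error rate bears on this point, so the check sets the sections side by side.

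**Step 1: apply the rescue statements to one child.** Take, as an illustration, a child with no fever or symptoms whose day-3 count is 40% of the day-0 count.

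| Protocol section | Trigger | This child |
|---|---|---|
| 4.3 | Day-3 count above 25% of day 0 | Early treatment failure |
| 4.2 | Treatment fails | Rescue |
| Rescue paragraph under 7.3 | Treatment failure within 14 days | Rescue |
| 8.2 | Early failure, or late clinical failure, within 14 days | Rescue |
| 6.7 | Clinical treatment failure within 14 days | Condition not met as worded |
| 7.3.1 | Symptomatic recurrence within 14 days | Condition not met as worded |

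The clearest mismatch is between 6.7 and 8.2, two sections with the same title.

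**Step 2: ask whether the count is known at the visit.** Under 8.3.1 this child's smear may be quantified later. From day 4 to day 14 the question does not arise for rescue. Failure in that window requires fever, a history of fever, danger signs or severe malaria, so the child is ill and 8.3.1 already has the smear read at the visit. The gap therefore concerns days 2 and 3.

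**Step 3: time to the next scheduled visit.**

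- After day 3 the next visit is day 7: 7 − 3 = 4 days.
- After day 2 the next visit is day 3: 1 day. That smear falls under the same reading rule.

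**Step 4: compare the reading rule with other procedures that need a prompt count.**

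- Section 7.3 requires extra blood when failure occurs after day 3 and density exceeds 10,000/mm3.
- Appendix I marks a venous draw on days 7, 14, 21 and 28, and at unscheduled visits, in cases of density above 10,000/mm3.
- The cryopreservation paragraph after 8.3.1 requires venous parasites from any late parasitologic failure. Section 4.3 defines that as day-28 parasitemia without fever.

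A draw that depends on a well child's smear result cannot be made at the visit if the smear is read afterwards. Section 8.3.1 therefore conflicts with these procedures as well as with 8.2.

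**Step 5: what does not change.** Section 8.3.1 has every smear quantified eventually. A child who meets a count criterion is an early failure under 4.3 whenever the slide is read, and both late parasitologic failure and adequate response exclude a child who has already met an early-failure criterion. That episode's 28-day outcome is fixed with or without rescue.

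**Step 6: how many children.** In the 2005 pilot the chloroquine arm had 105 − 25 = 80 known outcomes and 1 early failure, so 1/80 = 1.25%. The protocol does not say whether that failure was count-only, and it gives no count-only share for any arm. The number affected cannot be derived.

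**The case against.** The strongest reply is that deferred reading at efficacy visits was never intended. Section 8.3.1 is a general laboratory sentence, deferral is express only for four-weekly visits, and the sampling rules in step 4 make sense only if efficacy smears are read promptly. This is a fair account of what the authors probably meant, and standard operating procedures that are not shown may fix reading times. But no section states a reading time for days 2 and 3, and the general rule as written permits delay. The sampling rules show that 8.3.1 is mis-worded; they do not cure it.

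It can also be said that the rescue conflict is narrow. Neither 6.7 nor 7.3.1 says that rescue is given only in the case described, and three other statements agree. That stands, and it limits the point to a mismatch of scope. Staff working from 6.7 would still find no trigger for this child, while 8.2 tells them to act.

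A reader might infer more than the documents support:

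- *That late reading or inconsistent rescue alters the failure rates given to the DSMB.* It does not, for the reason in step 5.
- *That the day-3 child has a course cut short or is left on study drug.* Dosing ends on day 2, so on day 3 no dose is left to give or withhold.
- *That the plan has slides wait for days.* It states no interval. It only fails to exclude one.

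**Conclusion.** The point holds as a contradiction in wording with a safety consequence. The protocol does not give one answer on whether a well child with a count-only early failure receives rescue, and its general smear rule allows the deciding count to be unknown at the visit. The rule also conflicts with the protocol's own smear-dependent sampling.

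The effect is possible delay, up to 4 days to the next scheduled visit after a day-3 failure, and inconsistent use of rescue between children. A clinician is available daily, so a child who becomes ill may be seen sooner. The number of children is probably small, given 1 early failure among 80 in the pilot and the protocol's expectation of few early failures in every arm. This assessment assumes that no procedure outside the protocol already sets same-day reading.

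**What to change.** Two wording changes:

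1. In section 8.3.1, state that efficacy-visit smears on which a protocol action depends are read and quantified on the visit day. These are days 2 and 3 for early failure, and later efficacy visits where density or parasitemia triggers a blood draw. Limit later reading to the routine four-weekly visits, as 4.2 and 7.3 already describe.
2. Reconcile sections 4.2, 4.3, 6.7, 7.3.1, the rescue paragraph under 7.3, and 8.2 into one statement on whether a count-only early failure leads to rescue, and refer to it from the other places. Which clinical rule applies is for the sponsor to settle.

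The cost is an amendment and a same-day reading workload at the affected visits. The research clinic already has laboratory space for its microscopists, and the slides are the same ones read sooner. For days 2 and 3 the comparison with day 0 need not wait for a new blood count, because 8.3.1 bases density on days 0 to 3 on the day-0 white cell count.
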